##### **Secondary specific objective:**

- 3 Compare levels of breath hydrogen excretion among children taking FMSMS-RUTF or MSMS-RUTF to that of those taking P-RUTF.

#### **2.3.1.2 Specific objectives for efficacy trial**

The specific objectives (SOs) for the efficacy trial include the two primary objectives (1 and 2) and 16 secondary objectives listed below:

##### **Primary specific objectives:**

1. Compare the recovery rate of children aged 6-23 months with SAM treated with FSMS-RUTF with that of those treated with MSMS-RUTF and to that of children of same age treated with P-RUTF
2. Compare the recovery rate of children aged 24-59 months with SAM treated with FSMS-RUTF with that of those treated with MSMS-RUTF and to that of children of same age treated with P-RUTF

**Principal secondary specific objectives:**

- 1 Compare weight gain of children aged 6-59 months with SAM treated with FSMS-RUTF with that of those treated with MSMS-RUTF and to that of children of same age treated with P-RUTF (age group 6 to 23 months and 24 to 59 months to be sampled and analysed separately)
- 2 Compare time to recovery of children aged 6-59 months with SAM treated with FSMS-RUTF with that of those treated with MSMS-RUTF and to that of children of same age treated with P-RUTF (age group 6 to 23 months and 24 to 59 months to be sampled and analysed separately)
- 3 Compare height gain at 3 months after discharge of SAM children 6 to 59 months treated with FSMS-RUTF or MSMS-RUTF between them and to that of children of same age treated with P-RUTF (age group 6 to 23 months and 24 to 59 months to be sampled and analysed separately)
- 4 Compare deuterium dilution technique estimated body composition (Body Fat Mass, percentage body Fat Free Mass and lean mass) change at full recovery of children treated with FSMS-RUTF, MSMS-RUTF and P-RUTF
- 5 Compare change in phase angle over time of children treated with FSMS-RUTF, MSMS-RUTF, P-RUTF.

**Other secondary specific objectives:**

- 6 Compare the efficacy of FSMS-RUTF, MSMS-RUTF and P-RUTF in reducing the prevalence of anaemia among children recovering from SAM
- 7 Compare daily intake of RUTF in grams and in kcal/kg/day of children 6 to 59 months treated for SAM with FSMS-RUTF, MSMS-RUTF and P-RUTF (age group 6 to 23 months and 24 to 59 months to be sampled and analysed separately)
- 8 Compare breast milk intake of children 6 to 23 months old treated for SAM with FSMS-RUT, MSMS-RUTF and P-RUTF.
- 9 Compare proportion of children without intestinal inflammation as measured by stools calprotectin at 14 days, 28 days and recovery between SAM children treated with FSMS-RUTF, MSMS-RUTF and P-RUTF.
- 10 Compare recovery in level of plasmatic level of key growth related amino acid of children treated with FSMS-RUTF, MSMS-RUTF, P-RUTF and community controls.
- 11 Compare after discharge survival in SAM children treated with FSMS-RUTF, MSMS-RUTF, P-RUTF and community controls.

## 2.3.2 Hypotheses

The hypotheses for the objectives described above are as follows:

### 2.3.2.1 Phase 1: acceptability trial

#### Primary hypotheses:

- 1 FSMS-RUTF and MSMS-RUTF have organoleptic characteristics (taste, smell, texture, colour) as acceptable as the standard milk and peanut based RUTF (P-RUTF) for Malawian children aged 3 to 5 years attending community based child care centres (CBCC)
- 2 FSMS-RUTF or MSMS-RUTF intake will not be associated with more RUTF related side effects than P-RUTF in Malawian children aged 3 to 5 years attending CBCC.

#### Secondary hypothesis:

- 3 FSMS-RUTF and MSMS-RUTF will not be associated with a higher level of breath hydrogen excretion when compared to P-RUTF.

### 2.3.2.2 Phase 2: efficacy trial

#### Primary hypotheses:

- 1 Recovery rate of children aged 6 to 23 months with SAM treated with FSMS-RUTF is > 75% and is not inferior to that of children with SAM of the same age treated with MSMS-RUTF nor to that of P-RUTF with the fixed non-inferiority margin being 10%.
- 2 Recovery rate of children aged 24 to 59 months with SAM treated with FSMS-RUTF is > 75% and is not inferior to that of children with SAM of the same age treated with MSMS-RUTF nor to that of P-RUTF with the fixed non-inferiority margin being 10%.

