#### **1.5.3.2 Efficacy trial**

The sample size is calculated based on the primary objectives only. A minimum of 750 SAM children below 24 months of age and 450 SAM children 24 to 59 months of age is required to be 80% sure that the upper limit of a one-sided 95% confidence interval will exclude a difference in recovery rate in favour of the standard group of more than 10%. In addition 60 community control children will be enrolled for the Deuterium dilution technique sub-study. The number of children to be enrolled as community control of children discharged alive and for whom the follow up is possible will depend on the number of children meeting follow up eligibility criteria.

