## 2.5.3 Sample size and randomisation

### 2.5.3.1 Sample size

For the acceptability trial, a convenience sample of 20 children per group will be used. For assessing efficacy, the different sample sizes are calculated for a power of 80% and a level of significance of 0.05. The total sample size will be the total of sample required for the SO1 and SO2. For the other SOs, the calculated sample was lower than that required for the total sample for SO1 and SO2 as indicated in table 2 below.

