**Table 2: Sample size according to the specific objective for the efficacy study**

| Specific objective | endpoint                                           | Research design                   | Assumptions                                                                                                      | Calculated sample                               |
|--------------------|----------------------------------------------------|-----------------------------------|------------------------------------------------------------------------------------------------------------------|-------------------------------------------------|
| SO1                | Recovery rate
6-23 months                       | Non-inferiority
clinical trial | Recovery rate
P-RUTF, FSMS-RUTF, MSMS-
RUTF= 75.5%
Non-inferiority margin=10%
Loss to follow up =10% | 250 per arm.
Total=750 SAM children          |
| SO2                | Recovery rate
24-59 months                      | Non-inferiority
clinical trial | Recovery rate P-RUTF, FSMS-RUTF,
MSMS-RUTF = 88.2%
Non-inferiority margin=10%
Loss to follow up =10%    | 150 per arm.
Total=450 SAM children          |
| SO3                | Mean
weight gain
6-23 months                 | Non-inferiority
clinical trial | Standard deviation=4.1
non-inferiority margin =1.5g/kg/d
Loss to follow up=10%                             | 110 children/arm
Total=330 SAM children      |
| SO4                | Mean
weight gain
24-59 months                | Non-inferiority
clinical trial | Standard deviation=3.5
non-inferiority margin =1.5g/kg/d
Loss to follow-up=5%                              | 75 children/arm
Total=225 children           |
| SO5                | Mean
Length of stay
6-23 months              | Non-inferiority
clinical trial | Standard deviation=22.8
non-inferiority margin = 14 days
Loss to follow up=10%                             | 40 children/arm
Total= 120 children          |
| SO6                | Mean
Length of stay
24-59 months             | Non-inferiority
clinical trial | Standard deviation=9.9
non-inferiority margin = 14 days
Loss to follow up=10%                              | 30 children/arm
Total= 90 children           |

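### The stated 80% power is for one pairwise non-inferiority comparison; primary hypothesis 1 also requires a second comparator and recovery above 75%, at a planning rate of 75.5%

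*Protocol*

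**What the plan says.** The primary hypotheses appear twice in the same words, in the executive summary (Phase 2: efficacy) and in Section 2.3.2.2. For the younger age group: "Recovery rate of children aged 6 to 23 months with SAM treated with FSMS-RUTF is > 75% and is not inferior to that" of children of the same age "treated with MSMS-RUTF nor to that of P-RUTF with the fixed non-inferiority margin being 10" per cent. One sentence thus carries three conditions on FSMS-RUTF: recovery above 75%, non-inferiority to MSMS-RUTF, and non-inferiority to P-RUTF.

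Section 1.5.3.2 states the basis of sizing: "The sample size is calculated based on the primary objectives only". It then says that the sample "is required to be 80% sure that the upper limit of a one-sided 95% confidence interval will exclude a difference in recovery rate" of more than 10 points in favour of the standard group. Section 2.5.3.1 adds that "the different sample sizes are calculated for a power of 80% and a level of significance of 0.05".

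The SO1 row of Table 2 assumes 75.5% recovery in all three arms, a 10% margin and "Loss to follow up =10" per cent, and arrives at 250 per arm (750 in total). The binary formula printed below Table 2 compares one new treatment with one standard and has no term for a fixed threshold. Section 2.5.6.2.1 explains how confidence intervals are read against the margin and gives no rule for the 75% condition.

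**The concern.** The condition that looks least demanding is the hardest to meet. At the protocol's own planning value the FSMS-RUTF rate lies 0.5 points above the floor, while the standard error of one arm's rate is nearly 3 points. The requirement for two comparators lowers the chance of success further, and neither requirement enters the sizing.

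The younger group is the one for which the protocol says the formulation needed optimising (Sections 1.3 and 2.1), so this is the decisive stratum. A food exactly as good as P-RUTF at the assumed rate could clear both non-inferiority comparisons and still return an observed rate of, say, 74%. The protocol does not say whether that result confirms primary hypothesis 1. A reader who takes 80% as the chance of confirming it would be misled.

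**Working it through.** **Inputs.** True recovery 75.5% in every arm, margin 10 points, 250 per arm and 10% loss (Table 2, SO1); one-sided 95% limit and 80% power (Section 1.5.3.2); floor of 75% (Section 2.3.2.2). Evaluable per arm: 250 × 0.9 = 225.

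**1. The protocol's own figure.** The formula under Table 2 is n = f(α, β) × [πs(100 − πs) + πe(100 − πe)] / (πs − πe − d)². With one-sided 5% and 80% power, f = (1.645 + 0.842)² ≈ 6.18.

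- n = 6.18 × (2 × 75.5 × 24.5) / 10² = 6.18 × 36.995 ≈ 229 evaluable per arm.
- Allowing for 10% loss: 229 / 0.9 ≈ 255, or 229 × 1.1 ≈ 252. Both are close to the stated 250.
- One-sided 2.5% gives 291 (324 with loss) and does not reproduce 250.

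So 250 per arm is right for one pairwise comparison at one-sided 5%.

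**2. Distance to the floor.** SE of the FSMS-RUTF rate = √(0.755 × 0.245 / 225) = 0.0287. The gap of 0.005 is 0.005 / 0.0287 ≈ 0.17 SE. The exact binomial probability that the observed rate exceeds 75% is 0.589.

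**3. The conditions together.** They share the FSMS-RUTF arm and are correlated, so the probabilities cannot be multiplied. A simulation of 1,000,000 trials with three independent arms at 75.5% and unpooled Wald limits gives:

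| Condition (one-sided 5%) | 225 per arm | 250 per arm |
|---|---|---|
| Non-inferior to P-RUTF | 0.80 | 0.83 |
| Non-inferior to both comparators | 0.69 | 0.74 |
| P-RUTF only, and observed rate > 75% | 0.56 | 0.56 |
| Both comparators, and observed rate > 75% | 0.54 | 0.54 |
| Lower one-sided 95% limit > 75%, exact | 0.066 | 0.055 |
| Lower one-sided 95% limit > 75%, Wald | 0.089 | 0.073 |

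Adding non-inferiority to the last two rows changes them very little.

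**4. Where the loss comes from (225 per arm).** The second comparator costs 0.797 − 0.689 = 0.108. The 75% condition on the observed rate then costs 0.689 − 0.537 = 0.152.

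**5. Two-sided 95% limits.** The figure in Section 2.5.6.2.1 shows two-sided 95% intervals. If those were used, the figures at 225 per arm would be 0.70 (P-RUTF), 0.56 (both) and 0.48 (both, and observed rate > 75%).

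**6. Older age group.** With 88.2% assumed and 150 × 0.9 = 135 evaluable, the observed rate exceeds 75% with probability above 0.999.

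**The case against.** The best defence is that the protocol never claims 80% for the whole hypothesis. Section 1.5.3.2 ties the figure to excluding a 10-point difference, and for that event it is correct. Sections 1.5.1 and 2.5.1.2 describe a non-inferiority trial, the primary objectives (Section 2.3.1.2) say only that recovery will be compared, and the analysis section judges intervals against the margin alone. On that reading 75% is a benchmark, and a statistical analysis plan not at hand may say how it is judged.

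Much of this stands: there is no arithmetic error, and a benchmark reading is plausible. It does not remove the mismatch, because the protocol places the 75% condition inside the primary hypothesis, joined by a conjunction, and nowhere calls it descriptive. The requirement for both comparators is in the same sentence and is not open to a benchmark reading.

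Three stronger readings are tempting and are not supported:

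- **That the chance of success is only about 7%.** This needs a lower confidence limit above 75%, and the protocol nowhere states such a rule.
- **That the floor and the margin contradict each other.** With the comparator at 75.5% the margin alone would tolerate 75.5 − 10 = 65.5%, which the floor rejects. Both conditions can still hold together; the floor is simply the stricter one.
- **That the whole fall from 80% to 54% is due to the floor.** About 11 of the 26 points come from the second comparator.

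**Conclusion.** The point holds as a mismatch between a hypothesis and its sizing. At the protocol's planning rate, the chance of confirming primary hypothesis 1 as written is about 54% if the 75% condition is judged on the observed rate. Non-inferiority to both comparators alone has about 69%, and one comparison has the stated 80%. The floor is therefore a binding condition for which the trial has no planned power.

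These figures assume equal true rates of 75.5% in all arms, 225 evaluable children per arm and one-sided 5% limits. With all 250 evaluable, the 54% is unchanged and the 69% becomes 74%. A higher true FSMS-RUTF rate would ease the floor, but 75.5% is the protocol's own assumption. The problem with the floor is confined to ages 6 to 23 months. Enrolment, randomisation and the non-inferiority estimates are unaffected, so this should be fixed but does not threaten the trial.

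**What to change.** In the primary hypotheses (executive summary, Phase 2, and Section 2.3.2.2), state that 75% is a descriptive benchmark outside the confirmatory decision, and that FSMS-RUTF recovery will be reported with its confidence interval against it. In Section 1.5.3.2 and Table 2, state that 80% is the power for one pairwise non-inferiority comparison, and that for ages 6 to 23 months the power for both comparators together is about 69%.

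Whether to keep an absolute floor is the sponsor's choice. If it stays confirmatory, state that it is judged on the point estimate and restate the power of hypothesis 1 as about 54%. The figure of 56% would be wrong here, because it leaves out MSMS-RUTF.

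The cost is a less favourable stated power. Only wording changes; sample size and conduct stay as they are.

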#### Principal secondary hypotheses:

- 1 Weight gain (g/kg/day) during of children aged 6 to 59 months with SAM treated with FSMS-RUTF is not inferior to that of children with SAM of same age treated with MSMS-RUTF nor to that of those treated with P-RUTF with the fixed non-inferiority margin being 1.5g/kg/day (age group 6 to 23 months and 24 to 59 months to be sampled and analysed separately)
- 2 Time to recovery under treatment from admission to recovery of children aged 6 to 59 months with SAM treated with FSMS-RUTF is within the non-inferiority margin of 14 days when compared to children of the same age treated with MSMS-RUTF or to P-RUTF (age group 6 to 23 months and 24 to 59 months to be sampled and analysed separately).
- 3 Height gain during recovery and 3 months after discharge of children aged 6 to 59 months (admission age) with SAM treated with FSMS-RUTF is not inferior to that of children with SAM of the same age treated with MSMS-RUTF nor to that of children treated with P-RUTF given a fixed non-inferiority margin of 0.5 cm (age group 6 to 23 months and 24 to 59 months to be sampled and analysed separately)
- 4 Proportionally to body weight, percentage of body fat mass (BFM) measured at the time of recovery of children treated with FSMS-RUTF will not be higher than the percentage of BFM in children treated with MSMS-RUTF nor higher than the percentage of BFM of those treated with P-RUTF at the fixed margin of inferiority of 6%.
- 5 Tissues electrical properties assessed by Bio-electrical impedance analysis (BIA) will not be impaired in children treated with FSMS-RUTF when compared to that of children treated with MSMS-RUTF or with P-RUTF given a margin of equivalence to be determined by the synthesis methods based on findings of the SMS-RUTF study recently completed in DRC.

#### Other secondary hypotheses:

- 6 Haemoglobin gain of children treated for SAM with FSMS-RUTF will not be lower than that of children treated with MSMS-RUTF nor than that of those treated with P-RUTF given a margin of non-inferiority of 0.5g/dl.
- 7 The RUTF daily intake in grams and in kcal/kg/day of children 6 to 59 months old treated for SAM with FSMS-RUTF will not be inferior to the daily intake of children of the same age treated with MSMS-RUTF nor to the daily intake of those treated with P-RUTF given a margin of non-inferiority of 18g/day and 25kcal/kg/day, respectively (age group 6 to 23 months and 24 to 59 months to be sampled and analysed separately).
- 8 Breast milk intake of children 6 to 23 months old treated for SAM with FSMS-RUTF will not be lower than the breast milk intake of children of the same age treated with MSMS-RUTF nor to the intake of those treated with P-RUTF given a margin of non-inferiority of 100g/day.
- 9 Proportion of children with normalised stool calprotectin at 14 days, 28 days and recovery will not be lower in children treated for SAM with FSMS-RUTF than in those treated with MSMS-RUTF or in those treated with P-RUTF given a margin of non-inferiority determined using the synthesis method based on the confidence interval observed in children treated with P-RUTF.
- 10 Plasmatic level of key growth related AA of children treated with FSMS-RUTF will not be inferior to that of children treated with MSMS-RUTF or P-RUTF given a margin of non-inferiority defined using the synthesis method
- 11 12-months after discharge survival in children with SAM treated with FSMS-RUTF will not be inferior to that of children treated with MSMS-RUTF nor to that of those treated with P-RUTF given a margin of non-inferiority of 10%.

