### **Other secondary hypotheses:**

- 6 Haemoglobin gain of children treated for SAM with FSMS-RUTF will not be lower than that of children treated with MSMS-RUTF nor than that of those treated with P-RUTF given a margin of non-inferiority of 0.5g/dl.
- 7 The RUTF daily intake in grams and in kcal/kg/day of children 6 to 59 months old treated for SAM with FSMS-RUTF will not be inferior to the daily intake of children of the same age treated with MSMS-RUTF nor to the daily intake of those treated with P-RUTF given a margin of non-inferiority of 18g/day and 25kcal/kg/day (age group 6 to 23 months and 24 to 59 months to be sampled and analysed separately)
- 8 Breast milk intake of children 6 to 23 months old treated for SAM with FSMS-RUTF will not be lower than the breast milk intake of children of the same age treated with MSMS-RUTF nor to the intake of those treated with P-RUTF given a margin of non-inferiority of 100g/day.
- 9 Proportion of children with normalised stool calprotectin at 14 days, 28 days and recovery will not be lower in children treated for SAM with FSMS-RUTF than in those treated with MSMS-RUTF or in those treated with P-RUTF given a margin of non-inferiority determined using the synthesis method based on the confidence interval observed in children treated with P-RUTF.
- 10 Plasmatic level of key growth related AA of children treated with FSMS-RUTF will not be inferior to that of children treated with MSMS-RUTF or P-RUTF given a margin of non-inferiority defined using the synthesis method
- 11 12-months after discharge survival in children with SAM treated with FSMS-RUTF will not be inferior to that of children treated with MSMS-RUTF nor to that of those treated with P-RUTF given a margin of non-inferiority of 10%.

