Previous to the first randomised study conducted in Zambia, a formal acceptability and tolerance trial was conducted comparing SMS-RUTF and P-RUTF among 45 children aged 4-11 years. The SMS-RUTF was as acceptable as the P-RUTF with no associated adverse effects[90]. For the second randomised trial conducted in Democratic Republic of Congo (DRC), we assumed that the changes made to the formulation would not affect acceptability and tolerability. Thus, no formal acceptability trial was conducted. The results obtained regarding

frequency of diarrhoea, flatulence, vomiting, skin eruption and RUTF intake confirmed that SMS-RUTF was as accepted as P-RUTF (paper in preparation). The only difference observed was in intake and this difference was not of clinical relevance [214g/day (167kcal/kg/day) for P-RUTF versus 199g/day (152kcal/kg/day) for SMS-RUTF in children below 24 months and 276g/day (157kcal/kg/day) for P-RUTF versus 251g/day (139kcal/kg/day) for SMS-RUTF for children 24 months and more). For the present study, it is anticipated that the addition of the AA mixture will modify significantly the taste of the product. It is also well-known that the addition of milk powder makes the product sweeter.

Data on the efficacy of milk free RUTF in treating SAM in children are scarce. Valid has successfully conducted two randomised studies on the subject. These results showed that FSMS-RUTF was effective in children two years and above but not among children less than two years. [91]. Based on the results of that study, the formulation of FSMS-RUTF has been optimised

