### 2.3.3 Margin of non-inferiority

The margin of non-inferiority was fixed using the margin fixed method except for the secondary specific objectives 8, 15 and 16 of the efficacy trial, for which the synthesis method will be used. The margin for the recovery rate of 10% and of the time to recovery of 14 days were used in our previous study and was accepted by the reviewers of journals that have published the findings [15, 92]. All the other non-inferiority margin stated are based on the 95% confidence interval of the difference observed in our recent SMS-RUTF efficacy trial conducted in DRC (paper in preparation).

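### The two RUTF-intake margins, 18 g/day and 25 kcal/kg/day, do not agree with each other or with the protocol's own DRC figures, and their units may have been exchanged

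*Protocol*

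**What the plan says.** Hypothesis 7 among the other secondary hypotheses (Protocol 2.3.2.2) states: "The RUTF daily intake in grams and in kcal/kg/day of children 6 to 59 months old treated for SAM with FSMS-RUTF will not be inferior". The comparators are MSMS-RUTF and P-RUTF, and the thresholds are set by the clause "given a margin of non-inferiority of 18g/day and 25kcal/kg/day, respectively". The executive summary gives the same pair: "given a margin of non-inferiority of 18g/day and 25kcal/kg/day". The two age strata are kept apart ("age group 6 to 23 months and 24 to 59 months to be sampled and analysed separately"), but no age-specific intake margin is given.

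On the origin of the margins, section 2.3.3 justifies the recovery-rate and time-to-recovery margins by earlier use, assigns three objectives to the synthesis method, and then says: "All the other non-inferiority margin stated are based on the 95% confidence interval of the difference observed in our recent SMS-RUTF efficacy trial". The confidence intervals are not shown.

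Section 2.2 gives the DRC mean intakes in both units. The younger group's figures are "214g/day (167kcal/kg/day) for P-RUTF versus 199g/day (152kcal/kg/day) for SMS-RUTF in children below 24 months". Those of the older group read: "276g/day (157kcal/kg/day) for P-RUTF versus 251g/day (139kcal/kg/day) for SMS-RUTF for children 24 months and more". The section introduces both with the comment: "The only difference observed was in intake and this difference was not of clinical relevance".

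**The concern.** Intake in grams and intake in kcal/kg are two expressions of how much RUTF a child ate, the second standardised for body weight. Two margins for them need not be exact conversions of each other, but they should tolerate roughly similar losses, and both should be traceable to the stated source. Here a single gram margin and a single energy margin serve two age groups of quite different body weight. In the older group they also fall on opposite sides of the difference seen in the DRC trial.

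At stake is whether hypothesis 7 can be interpreted. A shortfall of the size seen in the DRC trial, which the protocol considers clinically unimportant, would rule out non-inferiority in grams in older children while possibly allowing it in kcal/kg/day. If a figure or unit was mis-transcribed, the hypothesis would be judged against a threshold nobody chose.

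**Working it through.** **Inputs.** Margins: 18 g/day and 25 kcal/kg/day (hypothesis 7). DRC means (section 2.2):

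| Age | P-RUTF | SMS-RUTF | Difference |
|---|---|---|---|
| 6-23 months | 214 g, 167 kcal/kg | 199 g, 152 kcal/kg | 15 g, 15 kcal/kg |
| 24-59 months | 276 g, 157 kcal/kg | 251 g, 139 kcal/kg | 25 g, 18 kcal/kg |

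**1. Can the margins be reproduced?** No. Their stated basis is a set of confidence intervals that the protocol does not print, and no standard deviation for intake is given. What can be checked is whether the two figures fit each other and the reported means.

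**2. Conversion by ratio of means.** Rate = mean kcal/kg/day ÷ mean g/day. Converted gram margin = 18 × rate. Leniency = 25 ÷ converted margin.

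| Age, food | Rate | 18 g equals | Leniency | 25 kcal/kg equals |
|---|---|---|---|---|
| 6-23, P-RUTF | 167/214 = 0.780 | 14.05 kcal/kg | 1.78 | 32.0 g |
| 6-23, SMS-RUTF | 152/199 = 0.764 | 13.75 kcal/kg | 1.82 | 32.7 g |
| 24-59, P-RUTF | 157/276 = 0.569 | 10.24 kcal/kg | 2.44 | 43.9 g |
| 24-59, SMS-RUTF | 139/251 = 0.554 | 9.97 kcal/kg | 2.51 | 45.1 g |

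**3. Conversion by ratio of arm differences.** A margin limits a difference, so this is a fair alternative.
- 6-23 months: 15/15 = 1.00, so 18 g equals 18.0 kcal/kg and leniency is 25/18.0 = 1.39.
- 24-59 months: 18/25 = 0.72, so 18 g equals 12.96 kcal/kg and leniency is 25/12.96 = 1.93.

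**4. Tolerated loss as a share of P-RUTF intake.**
- 6-23 months: 18/214 = 8.4% in grams; 25/167 = 15.0% in energy.
- 24-59 months: 18/276 = 6.5% in grams; 25/157 = 15.9% in energy.

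**5. DRC differences against the margins (point estimates).**
- 6-23 months: 15 < 18 g and 15 < 25 kcal/kg. Inside both.
- 24-59 months: 25 > 18 g, but 18 < 25 kcal/kg. Outside the first, inside the second.

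A confidence interval contains its point estimate. In the older group, therefore, 18 g could only be a limit on the near side of the estimate (smaller than 25), and 25 kcal/kg only a limit on the far side (larger than 18). The two cannot be the same kind of limit for that group. In the younger group both exceed the observed 15, so this argument excludes nothing there.

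**6. Exchanging the units.** The margins read 18 g and 25 kcal/kg; the older-group DRC differences are 25 g and 18 kcal/kg. With the units exchanged the pair would be 25 g and 18 kcal/kg.
- By P-RUTF means, 25 g equals 25 × 0.780 = 19.5 kcal/kg (younger) or 25 × 0.569 = 14.2 kcal/kg (older), against 18. The ratios are 18/19.5 = 0.92 and 18/14.2 = 1.27, instead of 1.78 and 2.44.
- By arm differences, 25 g equals 25.0 kcal/kg (younger) or 18.0 kcal/kg (older). The ratios are 0.72 and 1.00, instead of 1.39 and 1.93.

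**The case against.** Several objections are fair, and they limit the point.

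- **The scales are not one variable.** Energy per kilogram is standardised by each child's weight, and confidence limits on the two scales depend on their own variances. Exact conversion cannot be demanded, and nothing in the document is miscalculated. This stands: the issue is how the margins were chosen and whether they can be traced.
- **The size depends on the method.** The ratio of means turns the DRC differences of 15 g and 25 g into 15 × 0.780 = 11.7 and 25 × 0.569 = 14.2 kcal/kg, whereas the protocol's own differences are 15 and 18. Quoting only 1.8 and 2.5 would overstate the gap. This stands, so both conversions are given; the direction is the same under each.
- **Contradictory conclusions.** A reader might infer that the trial would report two conflicting verdicts on intake. The wording joins the scales with 'and', most naturally meaning that both margins must be met. Failing one then means the hypothesis is not shown. The gram margin would in practice govern, and the energy margin would add little.
- **The worked example uses point estimates of an earlier product.** Non-inferiority is judged by confidence interval, no intake variance is given, and the foods have been reformulated. A pass on energy is therefore only possible, not predicted.
- **The remark on clinical relevance** comes from a discussion of acceptability and sets no margin. Even so, it sits awkwardly with a gram margin smaller than that difference.

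None of this explains how 18 g/day follows from the stated source for older children.

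**Conclusion.** The concern holds in limited form: the two intake margins are not aligned with each other or with the protocol's DRC figures. The energy margin is about 1.4 to 1.8 times as lenient as the gram margin at 6-23 months and about 1.9 to 2.5 times at 24-59 months, depending on the conversion. This assumes that the DRC means describe the relation between the scales well enough for the present children.

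One part needs no conversion: 18 g/day lies below the older group's observed 25 g/day, so it cannot be the outer 95% limit for that group. Section 2.3.3 does not say which age group or which limit was used, so an origin in the younger group or in a pooled interval is not excluded.

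A reader might conclude that the units were certainly swapped. The documents do not establish this. The match in numbers is exact, but the matching figures are point differences, whereas section 2.3.3 refers to confidence intervals. It is a reason to check the source. Nor do the documents support reading this as a threat to the main result: intake is an 'other secondary' hypothesis, is not among the listed principal endpoints, and has no row in the sample-size table. Recovery rate, power and sample size are untouched.

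**What to change.** 1. Check both figures and their units against the DRC confidence intervals. State in section 2.3.3 which age group and which limit each comes from, and correct the margins if they were transposed. Do not simply swap the units: the exchanged pair equals the observed older-group differences and would still need justification as margins.
2. Before data are seen, choose one of two routes. Either set margins for each age group that agree across the two scales and say that both must be met, or name one deciding scale and report the other descriptively. Energy per kilogram is a reasonable candidate because section 2.5.4.3.2 prescribes the food in that unit, but the choice is partly preference.
3. Make the same change in the executive summary and in section 2.3.2.2.

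The cost is a wording change and a look at existing results, with no new data. The downside is that one stated margin changes or is given up.
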